## Abstract

**Background:**

Obesity during pregnancy is associated with adverse outcomes for the offspring and mother. Lifestyle interventions in pregnancy such as antenatal exercise, are proposed to improve both short- and long-term health of mother and child. We hypothesise that regular moderate-intensity exercise during the second half of pregnancy will result in improved maternal and offspring outcomes, including a reduction in birth weight and adiposity in the offspring, which may be protective against obesity in later life.

**Methods/Design:**

The IMPROVE (Improving Maternal and Progeny Risks of Obesity Via Exercise) study is a two-arm parallel randomised controlled clinical trial being conducted in Auckland, New Zealand. Overweight and obese women (BMI ≥25 kg/m2) aged 18–40 years, with a singleton pregnancy of <20 weeks of gestation, from the Auckland region, are eligible for the trial. Exclusion criteria are ongoing smoking or medical contra-indications to antenatal exercise.

Participants are randomised with 1:1 allocation ratio to either intervention or control group, using computer-generated randomisation sequences in variable block sizes, stratified on ethnicity and parity, after completion of baseline assessments. The intervention consists of a 16-week structured home-based moderate-intensity exercise programme utilising stationary cycles and heart rate monitors, commencing at 20 weeks of gestation. The control group do not receive any exercise intervention. Both groups undergo regular fetal ultrasonography and receive standard antenatal care. Due to the nature of the intervention, participants are un-blinded to group assignment during the trial.

The primary outcome is offspring birth weight. Secondary offspring outcomes include fetal and neonatal body composition and anthropometry, neonatal complications and cord blood metabolic markers. Maternal outcomes include weight gain, pregnancy and delivery complications, aerobic fitness, quality of life, metabolic markers and post-partum body composition.

**Discussion:**

The results of this trial will provide valuable insights on the effects of antenatal exercise on health outcomes in overweight and obese mothers and their offspring.

**Trial registration:**

Australian New Zealand Clinical Trials Registry ACTRN12612000932864.

## Background

The number of women entering pregnancy in an overweight or obese state has increased steadily in developed countries over the last three decades [1-4], and is also increasing in developing nations [5]. Maternal overweight and obesity are associated with adverse pregnancy outcomes, including higher risk of gestational diabetes, pre-eclampsia, operative delivery, fetal and perinatal mortality and morbidity, and excessive birth weight [6,7]. Maternal obesity can also result in long-term health problems for the offspring, secondary to perinatal problems and to intrauterine and postnatal programming effects [7,8], including an increased obesity risk in childhood and adulthood [9].

However, it may be possible to alter programming of the offspring of obese women to a healthier phenotype by interventions in pregnancy [10]. There is growing evidence to suggest the prenatal environment may play a role in programming obesity risk [11]. The link between maternal and offspring obesity can be explained by the ‘early-life hyper nutrition’ pathway where exposure to over-nutrition during fetal or early postnatal life may lead to perturbations of adipogenesis and/or appetite control mechanisms, creating a propensity to later obesity [8]. There is evidence from animal models that exposure to maternal obesity *in utero* can lead to offspring adiposity and cardiovascular and metabolic dysfunction, which may result from developmentally programmed hyperphagia, physical inactivity, and altered adipocyte metabolism [12]. Catalano postulates the existence of a vicious cycle of obesity, whereby maternal obesity leads to fetal overgrowth and subsequently post-natal obesity. Overweight/obese children tend to become obese adults, and the females, when pregnant, will increase nutrient supply to the fetus leading in fetal overgrowth in the next generation [13,14]. Further, it is proposed that offspring obesity may be propagated and enhanced in early life because of the abnormal metabolic milieu *in utero* in overweight and obese women [13,14]. This raises the potential of *in utero* therapy to prevent downstream obesity and chronic disease obesity in the offspring, via lifestyle interventions targeting behaviours that lead to altered nutrient partitioning and fetal overgrowth [10,13].

The effects of antenatal interventions on offspring outcome are difficult to establish. Birth weight is the most easily measured outcome assessing the impact of the intrauterine environment on fetal growth, [11] and we hypothesize that a reduction in fetal over-nutrition will be reflected as lower birth weight in offspring of overweight and obese mothers. The association between birth weight and adult weight suggests that there are enduring effects on later obesity risk [11], and we further postulate that reduction in birth weight will exert a protective effect on later obesity risk.

Antenatal exercise may play a positive role on both maternal and offspring health [15,16], and may be especially beneficial to the offspring of overweight and obese women [17]. While evidence on the effects of antenatal exercise on offspring outcomes (including birth weight) is inconsistent, there is no evidence of any adverse impact from moderate-intensity exercise [15,18]. Furthermore, the timing of antenatal exercise may be an important confounding factor leading to the varying effects of antenatal exercise on birth weight [17]. There is evidence that antenatal exercise in the second half of gestation can reduce fetal over-nutrition, birth weight and adiposity in the offspring, and protect against future obesity. Baraket et al. found that resistance exercise during the second and third trimesters of pregnancy attenuated the effect of increased maternal weight on offspring birth weight [19]. Clapp demonstrated that continuation of regular moderate- to vigorous-intensity antenatal exercise reduced offspring birth weight and subcutaneous fat mass at birth, with these potentially beneficial effects persisting up to 5 years of age [20], and that the maintenance of a high volume of exercise during mid and late pregnancy led to a reduction in fetal fat mass [21]. In a recent randomised controlled trial, we showed that non-weight-bearing aerobic exercise during the second half of pregnancy in non-obese women led to a significant reduction in offspring birth weight and BMI, in association with a reduction in metabolic markers of fetal nutrition [22].

Despite many studies investigating the effects of exercise during pregnancy, the effects of antenatal exercise in overweight and obese women on both short- and long-term health of the offspring are largely unknown. A recent systematic review of randomised controlled trials of antenatal exercise in overweight or obese women indicates that antenatal exercise may be beneficial in limiting gestational weight gain, but there is a lack of high-quality research evidence to assess the impact on offspring health [23]. Thus, the main aims of this trial are to establish if regular moderate-intensity, non-weight bearing exercise during the second half of pregnancy in overweight and obese women will reduce offspring birth weight and neonatal adiposity, and lead to long-term beneficial changes such as reduced obesity risk in the offspring. Secondly, we will explore the effects of antenatal exercise on fetal growth and body composition, maternal pregnancy and delivery outcomes, and maternal and cord blood metabolic and inflammatory markers. We will collect data on potential confounding/contributory factors including maternal weight gain, dietary intake, overall physical activity, physical fitness and quality of life indices during pregnancy.

## Methods/Design

The IMPROVE (Improving Maternal and Progeny Risks of Obesity Via Exercise) study is a two-arm parallel randomised controlled clinical trial being conducted in Auckland, New Zealand. This study is approved by the Health and Disability Ethics Committee (HDEC) (Ministry of Health, New Zealand; 12/NTB/24), and is registered with the Australian New Zealand Clinical Trials Registry (ACTRN 12612000932864). Locality approval has been obtained from the research offices at Auckland, Counties Manukau, and Waitemata District Health Boards, as well as relevant Māori research committees within the Auckland region.

### Participants

Pregnant women aged 18 to 40 years with a BMI ≥25 kg/m^2^ who are carrying a singleton fetus less than 20 weeks of gestation, with gestation confirmed by a dating scan early in pregnancy, and who are resident in the Auckland region are eligible for the trial. Exclusion criteria include ongoing smoking during the current pregnancy or contra-indications to aerobic exercise in pregnancy as stated by the American College of Obstetricians and Gynaecologists [24].

### Recruitment

The Auckland region has a population of approximately 1.4 million and approximately 21,000 births per year. Potential participants are idenified via maternity caregivers, posters and brochures in health care and community settings, and newspaper advertisements. All potential participants are supplied with detailed study information, and undergo an eligibility assessment. Eligible and willing participants are registered in the trial before completion of 20 weeks of gestation, and written informed consent obtained at the baseline visit. Target rate of recruitment is 8 participants per month, and recruitment is currently ongoing.

### Randomisation

After completion of baseline assessments, participants are randomised in a 1:1 ratio to either intervention or control group, using stratified blocked randomisation with variable block sizes of 2 and 4. The two stratification factors considered are parity (nulliparous/parous) and ethnicity (Maori/Pacific/New Zealand European or other).

Computer generated randomisation sequences have been provided by a biostatistician with no clinical involvement in the trial, and are stored securely in a password-protected computer. Once a participant is registered to the trial by the recruitment coordinator, a sequential study number and randomisation number is assigned to each participant. The recruitment coordinator does not have access to the randomisation tables. Group allocation is concealed until completion of baseline assessments.

### Intervention

The intervention group follow a regular structured exercise regime between 20 to 36 weeks of gestation, similar in nature to a previous antenatal exercise intervention conducted in non-obese women at our research institute [22]. The control group do not undergo any antenatal exercise intervention. Due to the nature of the intervention, participants are un-blinded to group assignment, following completion of baseline assessments.

The exercise regime consists of home-based stationary cycling. Magnetic exercycles (Sportop NB600/NB800) and heart rate monitors (Polar S625X/Polar RS800) are provided to each participant in the exercise group at 20 weeks of gestation. Exercise intensity is prescribed using target heart rate zones developed and validated specifically for overweight and obese pregnant women [25]. Participants receive instructions on equipment use and a written exercise prescription with weekly exercise targets. The 16-week exercise regime consists of 67 exercise sessions, comprising approximately 1500 minutes of moderate-intensity exercise. The frequency and duration of prescribed exercise varies over the intervention period. Participants are instructed to wear their heart rate monitors to record every prescribed exercise session they complete during the intervention period. This information is downloaded from each heart rate monitor to a computer at the end of the intervention period utilising Polar Precision Performance software (ProTrainer 5), so that compliance to prescribed exercise sessions can be assessed.

The intervention commences with 3 exercise sessions per week and increases to 5 sessions per week. All exercise sessions commence with a 5-minute warm-up on the stationary cycle at low intensity, maintaining heart rate below target rate, and concludes with a similar 5-minute cool down.The duration of moderate-intensity exercise at prescribed heart rate increases gradually from 15 minutes to 30 minutes per session and gradually decreases again from 33 weeks of gestation while maintaining the frequency at 5 sessions per week. A qualified exercise physiologist maintains regular contact with the exercising participants via phone, email, and home visits. To increase compliance with exercise, if cycling becomes unacceptable or uncomfortable with advancing pregnancy, participants are encouraged to utilise an alternative forms of exercise such as brisk walking, while maintaining same intensity, frequency, and duration of exercise.

Over the duration of the intervention period, both groups are free to continue their normal exercise/physical activity routines and receive standard antenatal care, and undergo similar study assessments. In addition, there are no dietary restrictions. Exercise participants developing obstetric contra-indications to exercise [24] will discontinue the exercise intervention, but be included in the intention to treat analysis.

### Primary outcome

Primary outcome is offspring birth weight, measured in grams (g) and standardized z-score (i.e. corrected for gestational age and gender) [26]. As there are significant differences in birth weight between major ethnic groups in New Zealand, birth weight will also be compared by customised centiles adjusting for maternal height, weight, parity, ethnic origin, gestational age at birth, and gender of the baby [27].

### Secondary outcomes

Offspring outcomes include neonatal anthropometry and body composition, fetal growth measures, cord blood metabolic markers and newborn complications including rates of large-for-gestational-age (birth weight >90^th^ centile) and small-for-gestational-age (birth weight <10^th^ centile) babies. Maternal outcomes include weight gain, aerobic fitness, quality of life, metabolic markers, post-partum weight and body composition, as well as pregnancy and delivery outcomes including timing and mode of delivery and length of hospital stay.

### Other aims and outcomes

This study also aims to establish a prospective mother-offspring cohort for follow-up to determine the long-term effects of antenatal exercise on anthropometry, body composition, and obesity risk.

### Clinical assessments/Data collection

Each participant visits the Maurice and Agnes Paykel Clinical Research Unit (Liggins Institute, Auckland) for three study assessments. The first visit for the baseline assessment occurs at 19 ± 1 weeks of gestation and the second visit at 36 ± 1 weeks of gestation. During the first visit, participants complete consent forms and fill in questionnaires on demographic, medical and obstetric history. The other procedures are similar for both first and second visits, where each participant’s weight, height, resting heart rate, resting blood pressure, HbA1c, and baseline aerobic capacity are assessed by a single investigator. Blood samples are collected and stored for metabolic testing. Participants complete a quality of life assessment questionnaire and the physical activity questionnaire and 3-day diet records are collected. At the second visit participants receive a pack with instructions for collection of cord blood by delivery staff.

During the intervention period, participants in both groups undergo regular ultrasound scans for research purposes at 4-week intervals starting from 24 ± 2 weeks of gestation. Participants are requested to maintain daily records of any leisure time physical activity/exercise they engage in between 20 weeks of gestation up to delivery on exercise diaries provided by the study. Participants also complete 3-day food intake records and a physical activity questionnaire at baseline prior to randomisation and midway though the intervention at a time when exercise prescription is maximal (32 weeks of gestation), to assess any group difference in these measures.

The final study visit occurs at 14 ± 2 days after delivery. Maternal weight and neonatal anthropometry (weight, length and occipito-frontal head circumference) are recorded, and both mother and baby have body composition assessed by DXA scans. Pregnancy, delivery and newborn data (including feeding history) are obtained from the participants and hospital records. Study exercise diaries and heart rate monitors are also collected at this point.

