### Antenatal measures - offspring

Measurement of fetal growth are performed using standard obstetric ultrasound techniques by a single investigator, blinded to group allocation, at a single medical institution in Auckland (Middlemore Hospital, Counties Manukau District Health Board). All scans are performed utilising a single Philips IU22 ultrasound scanner (Philips Ultrasound, Bothell, USA) with 3D capability. The ultrasound transducer adopted is the Philips curvilinear array (C5-1, Philips Ultrasound, Bothell, USA) while the 3D transducer is a mechanical curved-array 3D abdominal ultrasonic transducer (3D 6–2 Philips Ultrasound).

Standard growth measurements including biparietal diameter (BPD), head circumference (HC), humerus diaphyseal length (HDL), abdominal circumference (AC), and femur diaphyseal length (FL) are performed according to the protocols published by the Australasian Society for Ultrasound in Medicine [31]. At each examination, all measurements are obtained three times from three separately generated ultrasound images, and then averaged. The standard measurements are used to calculate estimated fetal weight (EFW) by the Hadlock 4 equation [32]. Scans are recorded electronically for later analysis of other measures of fetal growth and fat deposition. Soft tissue growth is assessed by measurements taken from the 3D volume dataset including thigh circumference (ThC), partial thigh volume (TVol), arm circumference, (ACirc) and partial arm volume (AVol) as described by Lee [33]. The 3D volume measurements are obtained by averaging three measurements from three manipulations of the one data set offline. Volume analysis is done offline using Philips QLAB™ software version 6. Measurements of fetal fat mass are calculated by taking the total cross-sectional limb area and subtracting the central lean area, as previously described [34].

Between-group comparisons of fetal growth will include measures of BPD, HC, AC, HDL, FL and EFW at 24, 28, 32, and 36 weeks of gestation. Between-group comparisons of fetal body composition will include measures of ThC, TVol, ACir, AVol and estimated fat mass at 28, 32, and 36 weeks of gestation.

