### Statistical considerations

#### **
*Sample size*
**

Based on a previous exercise intervention performed by our research group in Auckland using similar methodology [22] and using birth weight as the primary outcome, a total sample size of 100 women (n = 50 per group) will provide 80% power at 5% level of significance (two-sided) to detect a group difference of 250 g or more, assuming a standard deviation of 430 g [22].

#### **
*Data analyses*
**

Statistical analyses will be performed using SAS version 9.3 (SAS Institute Inc. Cary NC). All statistical tests will be two-tailed and a 5% significance level maintained throughout the analyses. Study data are entered into an Excel database, and then imported into SAS for final analysis.

#### **
*Baseline characteristics*
**

Baseline characteristics will be summarised using descriptive statistics. Continuous variables will be described as numbers of observed and missing values, mean, standard deviation, median, minimum and maximum. Categorical variables will be described as frequencies and percentages. Results will be presented for each of the two treatment arms as well as overall. Since any differences between randomised groups at baseline could only have occurred by chance, no formal significance tests will be conducted.

#### **
*Treatment effects*
**

Treatment evaluation will be performed on the principle of intention to treat (ITT), using data collected from all randomised participants. Analysis of covariance (ANCOVA) regression models will be used to evaluate the main treatment effect on the primary outcome between the two treatment groups, adjusting for parity and maternal ethnicity (i.e. stratification factors). A similar approach will be used for other continuous secondary outcomes, with the baseline outcome (if measured) added to the model as a confounding variable. Model-adjusted means and their difference between two groups will be estimated and tested. Logistic regression model will be used for the analysis of a binary outcome (i.e. yes or no), with associated odds ratio and 95% confidence interval. In addition to the intention to treat analysis, a per protocol (PP) analysis will also be undertaken on those participants who have no major protocol violations.

Reporting will adhere to the CONSORT guidelines for reporting parallel group randomised trials [35,36].

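### Fetal measures are compared at nominal weeks although scans may fall up to two weeks either side, and the stated model leaves out gestation at scan

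*Protocol article*

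**What the plan says.** **Scan timing.** Clinical assessments/Data collection states that "participants in both groups undergo regular ultrasound scans for research purposes at 4-week intervals starting from 24 ± 2 weeks of gestation", and places these scans in the intervention period. The Intervention section sets that period at 20 to 36 weeks. No separate window is given for the later scans.

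**Comparisons.** Under Antenatal measures - offspring, the arms are compared on "measures of BPD, HC, AC, HDL, FL and EFW at 24, 28, 32, and 36 weeks of gestation" and on "measures of ThC, TVol, ACir, AVol and estimated fat mass at 28, 32, and 36 weeks of gestation". A single blinded investigator performs the scans.

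**Model.** Under Statistical considerations (Treatment effects), the primary outcome is analysed by ANCOVA "adjusting for parity and maternal ethnicity (i.e. stratification factors". Then: "A similar approach will be used for other continuous secondary outcomes, with the baseline outcome (if measured) added to the model". A two-sided 5% level applies to all analyses.

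**Contrast with birth weight.** The Primary outcome section reports birth weight in grams and also as a z-score corrected for gestational age and sex. No such correction is stated for the fetal measures.

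**The concern.** Fetal size changes week by week, so a comparison at one nominal week is sharp only if the fetuses are close in age or age is in the model. The article allows a wide window for the first scan and carries it forward in 4-week steps. Its stated covariates do not include age at scan. The baseline term does not help: exercise starts at 20 weeks and the first scan falls at 22 to 26 weeks, so there is no pre-intervention fetal value to adjust for.

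At stake is the precision of an outcome set that the Discussion presents as a distinctive feature of the trial, in only 100 women. A real difference in growth could be missed because of avoidable noise. The article also lists many measure-by-week comparisons without naming a key fetal measure or week, so an isolated significant result would be hard to interpret.

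**Working it through.** **The plan's own figure.** The article gives no power figure for fetal measures. Its one calculation is for birth weight (difference 250 g, SD 430 g, 80% power, two-sided 5%): n per arm = 2 × (1.960 + 0.842)² × (430/250)² ≈ 46.4, so 47 (48 with the t distribution). The planned 50 per arm gives about 83% power (82% by the t-test), so it is slightly conservative. Only the 50 per arm is used below.

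**Step 1: ages at scan.** With exact 4-week steps:
- first scan at 22 weeks: 22, 26, 30, 34
- first scan at 24 weeks: 24, 28, 32, 36
- first scan at 26 weeks: 26, 30, 34, 38

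At each nominal week the ages can differ by up to 26 − 22 = 4 weeks, a full scan interval. If ±2 weeks applies to every scan separately, the possible spread is the same. The earliest and latest series contain no 36-week scan, and a 38-week scan falls after the period in which the scans are placed.

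**Step 2: share of variance due to timing, estimated fetal weight near 24 weeks.** Assumptions, none from the article: growth g of 10-18% per week, between-fetus CV 12%, and timing SD s of 0.5 weeks or 4/√12 = 1.155 weeks (even over ±2 weeks).

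Share = (g·s)² / [(g·s)² + 0.12²]

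| g per week | s = 0.5 | s = 1.155 |
|---|---|---|
| 10% | 0.0025/0.0169 = 15% | 0.0133/0.0277 = 48% |
| 15% | 0.0056/0.0200 = 28% | 0.0300/0.0444 = 68% |
| 18% | 0.0081/0.0225 = 36% | 0.0432/0.0576 = 75% |

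These figures cover one measure near one week.

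**Step 3: power, for any measure.** Let r be weekly growth divided by the between-fetus SD at fixed gestation, assumed to be 0.5 to 1.3. Without adjustment the SD grows by √(1 + r²s²). Take a difference detectable with 80% power when gestation is adjusted for: √(2/50) × (1.960 + 0.842) = 0.56 SD. Unadjusted power = Φ(2.802/√(1 + r²s²) − 1.960).

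| Spread of gestation at scan | r = 0.5 | r = 0.7 | r = 1.0 | r = 1.3 |
|---|---|---|---|---|
| even ±2 weeks (s = 1.155) | 68% | 59% | 45% | 34% |
| s = 1.0 | 71% | 63% | 51% | 40% |
| even ±1 week (s = 0.577) | 77% | 74% | 68% | 61% |

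Timing variance exceeds between-fetus variance only when r·s > 1, that is r above about 0.87 for the even ±2-week spread and above 1.0 for s = 1.0.

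**Step 4: number of comparisons.** 6 × 4 + 5 × 3 = 39. If each is tested at 5%, 39 × 0.05 = 1.95 false positives are expected when there is no effect, whatever the correlation. The chance of at least one is 1 − 0.95³⁹ = 86.5% under independence. By simulation with a common correlation of 0.3, 0.5, 0.7 or 0.9 it is about 74%, 57%, 37% or 18%.

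**The case against.** The best defence is that a condensed article is being read as a complete model. A similar approach is not a closed covariate list, the Discussion calls the scans longitudinal, and week-specific contrasts from a repeated-measures model would fit the listed comparisons. A fuller plan may add gestation at scan. This stands as far as it goes: the finding concerns the model as written. But the article does name covariates for this class of outcome, and it does correct birth weight for gestation, so the gap is in a stated choice.

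Three stronger readings are tempting and not supported:
- **A reader might infer that timing noise overwhelms any growth difference.** The article gives no growth rates, between-fetus SDs or actual scan dates. Under the assumptions above the loss runs from modest to severe.
- **A reader might infer that 39 separate tests will be run, each ignoring that the same fetus is scanned repeatedly.** The article lists comparisons; it does not state one test per measure and week. The count would also change if fat mass were analysed separately for arm and thigh. The measures are correlated (estimated fetal weight is calculated from the standard measurements), so 86.5% is an upper-end figure.
- **A reader might infer bias.** Allocation is randomised and the sonographer is blinded, so the expected harm is lost precision, unless scan timing comes to differ by arm.

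It is also fair to say that the 22- and 26-week starts are the ends of the window. If most first scans fall close to 24 weeks, the loss is small.

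**Conclusion.** The point holds as a loss of precision in secondary outcomes. Followed as written, the plan compares fetuses that may be up to 4 weeks apart in age without adjusting for that age. For estimated fetal weight near 24 weeks, timing would be 15-36% of variance at a timing SD of 0.5 weeks and 48-75% for an even ±2-week spread, given a 12% CV and growth of 10-18% per week. More generally, a comparison with 80% power under adjustment would fall to 34-68% for an even ±2-week spread and to 61-77% for ±1 week, if weekly growth is 0.5 to 1.3 between-fetus SDs. All these inputs are assumptions, but every scenario computed loses power. The multiplicity point is conditional on separate testing and matters for interpretation only. The primary birth-weight test is untouched. The change is worth making because it improves precision at almost no cost.

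**What to change.** - Include exact gestational age at scan in the analysis of every fetal measure. Preferably fit one linear mixed model per measure to all scans, with gestation as continuous time, arm, arm-by-gestation, parity and ethnicity, and a random effect for the fetus. Gestation-specific z-scores, as already used for birth weight, are an acceptable alternative.
- Report one trajectory test per measure, with the estimated difference between arms at 36 weeks and its 95% CI. This gives 6 + 5 = 11 tests. At 5% each, 0.55 false positives are still expected with no effect, so label these results secondary or exploratory.
- Reconcile Clinical assessments/Data collection with Antenatal measures - offspring: state the window for each scan and how a scan is assigned to a nominal week, if nominal weeks are kept.

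The cost is analysis-plan wording and slightly more programming. No new data are needed: eligibility requires gestation confirmed by an early dating scan, and the study scans are recorded electronically.
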